#### Self-efficacy

Self-efficacy is a perception of a patient’s ability to engage in the skills necessary to master a new challenge when facing obstacles. An IBD-specific self-efficacy scale has been developed (Table S10 in Multimedia Appendix 1). The 29-item instrument includes questions on managing medical care, stress and emotions, and symptoms and disease, as well as maintaining remission. Responses range from 1=not sure at all to 10=totally sure. Scores range from 29 to 290, with higher scores correlating with greater self-efficacy [49].

#### Health Care Use

Health care use will be measured using the Canadian Community Health Survey (Table S11 in Multimedia Appendix 1).

### Data Management

Outcome measures from participants will be collected via direct data capture through use of electronic data entry forms sent to participants via email. Information on health care use will be collected by research staff at each site and recorded in the source documents. The data will then be entered electronically into electronic case report forms. All data will be maintained, archived, retrieved, and distributed by a computer system.

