### Study Conduct

Eligible patients will be approached by research staff at the time of routine clinical visits or via telephone and provide informed consent. All of the participants’ concomitant medications will be continued during the study. Corticosteroids will be tapered at the discretion of the investigator. Addition of new IBD medications will be allowed during the study. If the new medication is an eligible oral or subcutaneous addition to existing therapy, this will be tracked using the approach that was used to track the original medication during the initial treatment. If the new medication replaces the initial therapy, the replacement medication will be similarly tracked.

Participants will be randomized 2:1 to receive either remote monitoring or standard of care using a random permuted block design with randomly varied block sizes. Participants will be stratified based on study site and disease subtype (CD vs UC or indeterminate colitis). We chose to stratify on these variables because they could affect the response to the intervention; stratification will ensure balance of these covariates among the study groups. The randomization order will be computer generated, and group assignment will be made when a new participant is enrolled into the study by the clinical site. The site investigators and research staff will remain blinded to the randomization order. The participants and physicians will not be blinded to the group assignment; however, we will attempt to minimize measurement bias by collecting outcome data through electronic data capture directly from participants.

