At the time of taking a medication dose, participants will scan the label with their mobile phone to verify that they are taking the medication. Upon scanning, participants will immediately receive a notification on their device indicating that the label was successfully scanned and that their medication adherence was updated in their profile. Each day that a medication is due to be taken, participants will receive a reminder through SMS text message notifying them of their medication schedule for the day. If participants fail to scan the label at a given time (as determined by their specific medication regimen), they will receive an SMS text message at the end of the day with a link to respond to a survey that captures reasons for nonadherence.

Participants will also complete a PRO-2 assessment at baseline and then monthly for the entire 12 months of the study triggered by the Tappt system through an HTML link sent to patients by SMS text message [31,32]. For participants with CD, the PRO-2 assessment includes abdominal pain and liquid stool frequency. For participants with UC or indeterminate colitis, the PRO-2 assessment includes rectal bleeding and stool frequency. The research team will also be able to send the PRO-2 survey to patients at any given time, at their discretion, if patients are experiencing a flare or at the time of a change in medication dose. Items for the PRO-2 assessment vary based on disease type (refer to the Outcomes and Outcome Measures section).

Clinical teams can review their participants’ data in real time through the secure cloud-based provider-facing Tappt portal. To reduce monitoring burden among clinical teams, the system’s algorithms prompt automated email alerts to the clinical team when participants’ adherence or PROs fall below predetermined thresholds, when a participant’s regimen is approaching refill date, or when a participant reports an error on their profile. These alerts can support clinical teams in following up with patients in a timely manner to reduce risk for poor outcomes (Figure 1).

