### Outcomes and Outcome Measures

#### Overview

The outcome measures outlined in the following sections will be assessed at baseline and at 12, 26, and 52 weeks after initiating treatment. All outcome measures will be captured electronically and will not require a study or office visit.

The primary outcome of the proposed study will be the difference in mean MPR between the intervention and control groups during the 12-month study. The mean MPR will be calculated as follows:

MPR = number of days’ supply of medication obtained during observation period / total number of days in observation period.

If a participant discontinues therapy but initiates treatment with another eligible medication, the MPR will continue to be calculated. Any delay in initiating new treatment will be adjusted for the total number of days in the observation period (ie, if drug A is discontinued and drug B is started 2 weeks later, the observation period will be 365 – 14 = 351 days); for example, if a participant is prescribed oral mesalamine (1.2 g), 4 tablets daily, for 90 days (dispense 360) with 2 refills between months 6 and 12, the MPR would be 100%. Likewise, if a participant is prescribed ustekinumab 90 mg subcutaneous every 8 weeks (dispense 1 syringe) with 2 refills between months 6 and 12, the MPR would be 66%. Data on medication use will be self-reported by participants at each time point. However, we will randomly validate participant report via chart review of pharmacy data for 20% of the participants. Participants will report the date the medications of interest were filled as well as the number of days’ supply of medications filled. Self-reported adherence will be assessed with the Medication Adherence Report Scale-5 questionnaire (Table 2). Scores for each item are summed to give a total score, with higher scores indicating higher levels of reported adherence [33].

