The secondary outcome of the proposed study will be the difference in health care use between the intervention and control groups during the 12-month study. For health care use, we will use a composite end point, including counts of hospitalizations, urgent care or emergency room visits, IBD-related surgeries, telephone calls (primary care and IBD provider), endoscopic procedures, imaging examinations, and blood and stool testing. We will also assess new prescriptions for corticosteroids (prednisone and budesonide) at each time point during the study period. The total events will be adjusted per 100 patient years of follow-up because the 2 groups will be unequal in number. In addition, we will evaluate each outcome individually. The relatedness of hospitalization and urgent care or emergency room visits to IBD will be determined as well. Information will be obtained from patient self-report at each assessment. This approach has been validated in patients with IBD using a modification of the Canadian Community Health Survey [34]. However, we will validate participant self-report via chart review for 20% of the participants, randomly selected.

**Table 2 table2:** Medication Adherence Report Scale-5 questionnaire.

Item	Scoring				
	Always	Often	Sometimes	Rarely	Never
I forget to take my medication	1	2	3	4	5
I alter my medication dose	1	2	3	4	5
I stop taking my medication for a while	1	2	3	4	5
I decide to miss out a dose of my medication	1	2	3	4	5
I take less medication than instructed	1	2	3	4	5

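### Data Management has site research staff collect health care use, whereas Table 1 and the outcome section have participants report it, under an electronic-capture safeguard

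*Protocol article*

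**What the plan says.** The Overview under Outcomes and Outcome Measures names the outcome: "The secondary outcome of the proposed study will be the difference in health care use between the intervention and control groups". It gives the source as "Information will be obtained from patient self-report at each assessment", says this approach has been validated in IBD with a modified health survey, and adds chart review of a randomly selected 20% as a check on self-report. The short Health Care Use section names the survey. Table 1 lists the patient as the source, at baseline and weeks 12, 26 and 52.

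On mode of capture, the same Overview says "All outcome measures will be captured electronically and will not require a study or office visit". Study Conduct, having said that participants and physicians are not blinded, adds: "we will attempt to minimize measurement bias by collecting outcome data through electronic data capture directly from participants".

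Data Management begins in agreement: "Outcome measures from participants will be collected via direct data capture through use of electronic data entry forms sent to participants via email". It then treats health care use separately: "Information on health care use will be collected by research staff at each site and recorded in the source documents". Entry into electronic case report forms comes afterwards.

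**The concern.** A site that follows Data Management and a site that follows Table 1 and the Overview would collect the named secondary outcome in different ways. In the first case, a person who knows the arm stands between the participant and the record. In the second, the participant completes the same form on the same schedule whichever arm was assigned.

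The safeguard is what is at stake. With assignment open, direct electronic capture is the only measure that the article offers against measurement bias, and the Data Management sentence takes health care use out of it. There is also a consequence for the chart check. If staff draw the information from records, a 20% chart review described as validating self-report no longer tests the data that are analysed.

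**Working it through.** There is no planned figure to reproduce for this point. The sample size of 123 rests on adherence rates for the primary outcome and does not change whichever source is used. The check is a comparison of the text.

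1. **Who is the informant?** Table 1 separates patient-sourced rows from rows sourced from the provider or site. Clinical history, C-reactive protein, calprotectin and both endoscopic scores are in the second group; health care use is in the first. The Overview agrees with Table 1. Data Management names research staff as collectors and does not say from whom they obtain the information.

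2. **How is it captured?** The Overview says that all outcome measures are captured electronically, and Study Conduct relies on capture directly from participants. Data Management describes a different route for health care use: staff, then source documents, then case report forms. The preceding sentence in that section has just described direct participant entry, so health care use is set apart from it.

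3. **Can the 20% chart review explain the sentence?** No. The sentence carries no 20% limit and does not mention validation. It describes how the outcome is collected in general.

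4. **Can a mild reading remove the conflict?** Suppose that staff administer the survey and transcribe the answers. The participant is then still the informant, which satisfies Table 1 and the source statement in the Overview. Direct electronic capture is still lost, contrary to the Overview's general rule and to Study Conduct. The conflict on mode survives this reading. The conflict on source is possible but not certain.

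5. **Do research staff know the arm?** The document does not say so outright, but it follows. Study Conduct blinds site investigators and research staff to the randomization order only. Under Intervention Group, the research team trains intervention participants, enters their regimens and assigns their labels.

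6. **Is staff contact equal between arms?** No. Besides the training and set-up, coordinators check weekly for dose changes in intervention participants. The Control Group section describes no counterpart.

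Steps 5 and 6 give a plausible route by which collection by staff could differ between arms. They do not show that it will, or by how much.

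**The case against.** The strongest reply is that Data Management says who gathers and records the information, not who supplies it. Table 1, the Overview and the named survey all point to the participant, and an article need not spell out who administers a survey. This stands as far as the source is concerned: two separate data streams are not proven. It does not answer the conflict on mode, because the article states both procedures itself and they are incompatible.

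A second reply is that the Study Conduct safeguard does not mention health care use and was never universal, since laboratory and endoscopic measures come from the site. That is correct. Table 1 nevertheless places health care use among the patient-sourced outcomes, where the safeguard would be expected to apply.

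A reader might go further and infer that staff are bound to hear of more events in the intervention arm through the portal and the alerts. The documents do not support this. The statement "Clinical teams can review their participants’ data in real time" concerns clinical teams. The portal is described as showing medication intake, barriers and patient-reported outcomes, not hospital stays, imaging or tests. Alerts are followed up by a clinical nurse, pharmacist or social worker. The weekly check concerns dose changes. Nor does any passage prescribe different collection by arm.

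It is also fair to say that participants are unblinded, so self-report is not masked ascertainment. Its advantage is narrower: one instrument and one schedule, applied without an intermediary who knows the arm. Finally, the chart check loses its purpose only if staff take the data from records; if they transcribe participants' answers, it still validates self-report.

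**Conclusion.** The point holds as an internal contradiction about the named secondary outcome. It is certain for the mode of capture and possible for the source. The risk of differential ascertainment is a reasonable inference, resting on two things: that research staff know the arm, and that their greater contact with intervention participants could affect what they record.

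The size of any bias cannot be derived from the document. It gives no event rates for health care use and no capture rates by source, so any percentage would be invented. The primary outcome and the sample size are unaffected. The sentence should be corrected before data collection, but this is not a flaw that undermines the trial.

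**What to change.** Correct the health care use sentence in Data Management so that, in both arms, this outcome comes from the electronic survey completed by participants at baseline and weeks 12, 26 and 52, in line with Table 1 and the Overview. State that the staff role for this outcome is limited to the random 20% chart validation already planned.

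The cost is a change of wording. The survey, the schedule and the chart check are all in the plan, so no new procedure is needed. Masking the chart reviewers to arm is not needed to resolve the contradiction, and it would be an addition to the plan.

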### Statistical Analyses

Baseline analyses will include tabulations of demographic and clinical variables of the study participants. Chi-square tests and 2-tailed *t* tests will be used to compare these groups to determine whether baseline differences exist. The distribution of each continuous variable will be inspected for outliers to determine whether a parametric or nonparametric approach should be applied. The Wilcoxon rank sum test will be used for any variable that does not meet the statistical assumptions of the *t* test. In addition, analyses will be conducted stratified by clinical site to determine whether the sites are comparable across the groups of interest. If differences are detected, these variables will be evaluated as potential confounders in the regression models.

For study aim 1, we will compare the mean MPR ratio between the intervention and standard of care groups using *t* tests. For study aim 2, we will compare differences in health care use between the groups using the Wilcoxon ranked sum test because we expect that the data will not be normally distributed.

For the secondary aims of clinical outcomes and health care use, dichotomized outcomes will be compared in a similar fashion with bivariate analyses. For health care use, the outcome will be investigated in quartiles of health care use, and specific outcomes of interest selected a priori will be investigated (eg, need for hospitalization for IBD, need for IBD surgery, and initiation of corticosteroids).

All analyses will be completed using intention-to-treat principles. Assuming 2 intervention participants for every 1 control, with adherence rates of 0.65 among controls and 0.9 in intervention participants and with a type I error rate of 0.05 and power of 0.9, we will need to enroll 123 participants: 82 (67%) in the intervention group and 41 (33%) controls. We may enroll more patients pending our initial recruitment and data capture.

Although we will make every effort to obtain complete data from all randomized participants, we anticipate that there could be as much as 20% loss to follow-up by 12 months. To detect potential bias by analysis of only the collected data, we plan first to compare patients with data with those without data at a given time point on baseline characteristics to determine characteristics of those who do not provide complete data. We will also perform sensitivity testing to see whether estimates of intervention effects differ if only patients with complete data are analyzed. Depending upon the extent of missingness, we will also consider imputation methods that use multiple regression predictions for imputation.

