## Introduction

### Background

Inflammatory bowel diseases (IBDs), comprising Crohn disease (CD) and ulcerative colitis (UC), are chronic, progressive, inflammatory conditions of the gastrointestinal tract that affect up to 3 million Americans [1]. IBD is thought to be driven by inappropriate immune responses to an altered gut microbiome, with a disease course characterized by remitting and relapsing episodes of inflammation, or flares.

Most patients with a chronic condition require long-term therapy. Evidence has demonstrated that suboptimal adherence is associated with poor clinical outcomes, including increased IBD activity and associated complications, worsened quality of life (QoL) [2], and higher health care use and costs [3]. In addition, nonadherence to biologic therapies may increase the risk for developing antidrug antibodies, leading to loss of response to therapy. Despite this, adherence to IBD therapies remains suboptimal. A recent survey administered to 322 patients with IBD found that 55% reported nonadherence, including forgetting or skipping medication owing to not feeling well [4]. Overall adherence to IBD medications ranges from 40% to 80%, depending on the patient population, medication class, data sources, and adherence quantification measures [5].

Adherence to oral IBD medications such as aminosalicylates and thiopurines ranges from 50% to 93% [6]. Studies evaluating adherence to biologic therapies are conflicting. Using a medication possession ratio (MPR)—calculated as the number of days of supply of medication obtained during the observation period out of the total number days in the observation period—of <100% as a definition of nonadherence in 365 patients with IBD treated with biologic therapies, adherence was highest for intravenous formulations (70%-83%) compared with subcutaneous biologics (47%-50%) [7]. Conversely, in a large multicenter prospective cohort study where adherence was defined as ≥80% using a visual analog scale, the majority of patients with CD and UC were considered adherent (88% and 86%, respectively) [8]. However, when comparing across medication classes, adherence was lowest for patients on rectal (68%) and oral (83%) therapies and highest for intramuscular (88%) and parenteral (87%) therapies [8]. Similar results were found in a recent study of 112 patients with IBD in the Manitoba cohort: 81% of the patients were considered adherent to their therapy using an MPR cutoff value of ≥90% [9].

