### Study Population

Patients will be recruited for this study from 5 clinical centers at the University of Maryland School of Medicine, University of Cincinnati School of Medicine, NYU Grossman School of Medicine, University of North Carolina School of Medicine, and Vanderbilt University School of Medicine.

Inclusion criteria will include (1) aged ≥18 years; (2) documented IBD based on usual diagnostic criteria, including clinical symptoms and findings from endoscopy, radiology studies, and histology [30]; (3) initiation of treatment with a new oral or subcutaneous treatment for IBD; (4) access to a smartphone with a reliable data plan or Wi-Fi access; and (5) ability to understand the protocol and provide informed consent in English. Exclusion criteria will include (1) inability to speak and read English or comply with the study protocol; (2) the presence of an ileostomy, colostomy, ileoanal pouch anastomosis, or ileorectal anastomosis; (3) initiation of oral corticosteroids only without concurrent use of an oral or subcutaneous maintenance therapy; (4) imminent surgery within the next 60 days; (5) history of short bowel syndrome; or (6) uncontrolled medical or psychiatric disease.

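### The primary t test leaves out the two randomisation strata, and a separate rule lets tests of baseline differences nominate covariates: efficiency may be forgone, but validity is not lost

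*Protocol article*

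**What the plan says.** **Design.** Study Conduct: "Participants will be stratified based on study site and disease subtype (CD vs UC or indeterminate colitis". The reason follows: "We chose to stratify on these variables because they could affect the response to the intervention". Study Population: "Patients will be recruited for this study from 5 clinical centers". Five sites by two subtypes makes ten strata.

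**Primary outcome and analysis.** Outcomes and Outcome Measures, Overview: "The primary outcome of the proposed study will be the difference in mean MPR between the intervention and control groups during the 12-month study". Statistical Analyses: "we will compare the mean MPR ratio between the intervention and standard of care groups", with t tests as the method. Site and subtype are not named in that comparison. Of the secondary aims, the section says "dichotomized outcomes will be compared in a similar fashion with bivariate analyses".

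**Covariates.** Statistical Analyses first plans chi-square and t tests of baseline variables between the groups, then analyses by site as a check of comparability. It continues: "If differences are detected, these variables will be evaluated as potential confounders in the regression models". The article describes no regression model for MPR. The by-site analyses are not presented as a stratified estimate of the treatment effect, and no other section commits to adjusting for the strata.

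**The concern.** There are two linked problems.

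1. **Analysis does not follow design.** Stratified blocks force the arms to be balanced on site and subtype. If those factors predict MPR, the true sampling variance of the difference in means is smaller than the variance the t test estimates, because the test still counts between-stratum variation as noise. The interval is then wider than it need be, and the test rejects a true null less often than 5%.

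2. **Covariates nominated by significance tests.** Under randomisation a baseline difference between arms is a chance event. A test of it says nothing about whether the variable predicts the outcome. A strongly prognostic variable that happens to be balanced is passed over, and an irrelevant one that happens to be unbalanced is taken up. Since the regression models are not specified, a reader also cannot tell what standing an adjusted MPR estimate would have beside the t test.

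At stake is some precision in a trial of 123 patients that expects up to 20% loss to follow-up, and clarity about which estimate is the result.

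**Working it through.** **Does the sample-size statement supply what is needed?** Inputs from Statistical Analyses: 0.65 against 0.90, 2:1 allocation, alpha 0.05, power 0.9. With pooled proportion (0.65 + 2 × 0.90)/3 = 0.8167:

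n(control) = [1.960 × √(1.5 × 0.8167 × 0.1833) + 1.282 × √(0.65 × 0.35 + 0.90 × 0.10/2)]² / 0.25² = (0.929 + 0.669)² / 0.0625 = 40.9, so 41 + 82 = 123.

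The figure reproduces (two-sided, no continuity correction). It is a calculation for two proportions, so it yields neither an SD for MPR nor an R2. Both are assumptions below.

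**Assumptions.** SD 0.25 and difference 0.135, which put the t test at about 80% nominal power with 82 and 41 patients. R2, the share of within-arm MPR variance explained by site and subtype, ranges from 0 to 30%.

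**Approximation, taking the strata as perfectly balanced.** Nominal SE = 0.25 × √(1/41 + 1/82) = 0.0478, and 0.135/0.0478 = 2.823. With s = √(1 − R2):

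- width of unadjusted interval relative to adjusted = 1/s
- true type I error of the t test = 2 × [1 − Φ(1.96/s)]
- power of the t test = Φ((2.823 − 1.96)/s)
- power of the adjusted analysis = Φ(2.823/s − 1.96)

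| R2 | Width ratio | Type I error, t test | Power, t test | Power, adjusted |
|---|---|---|---|---|
| 0% | 1.00 | 5.0% | 80.6% | 80.6% |
| 2% | 1.01 | 4.8% | 80.8% | 81.4% |
| 10% | 1.05 | 3.9% | 81.9% | 84.5% |
| 20% | 1.12 | 2.8% | 83.3% | 88.4% |
| 30% | 1.20 | 1.9% | 84.9% | 92.1% |

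**Simulation, allowing for incomplete blocks** (N = 123, ten strata, 2:1 permuted blocks). For R2 of 10/20/30%, type I error of the t test was 4.6/3.4/2.2%. Power was 81/82/84% unadjusted and 84/87/91% adjusted. A further run of 6,000 replicates per setting, with blocks of 3 or 6, gave 4.2/3.0/2.5%, with power 80/82/83% against 83/88/91%. In that run the adjusted model held its level (5.1-5.2%), and at R2 of 0-2% the two analyses differed in power by at most 0.5 points.

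**Baseline tests.** The number of tests is not stated. For an assumed 15 to 20 independent tests at 5%, the chance of at least one false flag is 1 − 0.95^15 = 54% to 1 − 0.95^20 = 64%. Correlated variables, such as the PROMIS domains, would change this, so it is only an illustration.

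**The case against.** The best defence is that the harm may be negligible. The article justifies stratification by a possible effect on response to the intervention, which read literally is effect modification and not prognosis. Its one adherence contrast by subtype (Background: 88% in Crohn disease, 86% in ulcerative colitis) implies, with equal groups, R2 = 0.01²/(0.87 × 0.13), about 0.1%. It gives no figure by site. That contrast concerns a binary visual-analog measure, so it is only a guide to MPR, but it rules out confidence in a large effect. This stands, and it is why the range must start at zero.

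Several stronger readings are tempting but are not supported:

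- **That the t test is invalid or underpowered against its nominal figure.** It errs on the conservative side. In the table its power is never below the 80.6% nominal value; what is lost is a possible gain.
- **That the primary estimate is itself data-driven.** A t test has no covariates. The selection sentence concerns separate models, and flagged variables are to be evaluated, not automatically entered.
- **That the interval is too narrow because the variances are unequal.** This needs a pooled-variance test, which the article does not specify, and an assumed pair of SDs. A Welch test would keep coverage at about 95%.
- **That the Background shows route must be a covariate.** The contrast "adherence was highest for intravenous formulations (70%-83%) compared with subcutaneous biologics (47%-50" involves intravenous therapy, which is not an eligible study treatment. The other class figures are oral 83% against parenteral 87% and intramuscular 88%, a small gap.
- **That the earlier UC HAT trial proves the point.** The article attributes that imbalance to inadequate randomisation and locates it in immune suppression use and quality of life. Adjusting for site and subtype would address neither.

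The article is also condensed, and model details may properly sit in a fuller plan. But the t test and the selection rule are stated choices, not omissions.

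**Conclusion.** The point holds as one of efficiency and prespecification. The design stratifies on two factors, the stated primary analysis uses neither, and a stated rule lets chance differences nominate covariates for undefined models. The size depends wholly on an R2 that the documents do not give: nothing material at 0-2%, and about 3 to 8 points of power forgone at 10-30% under SD 0.25 and difference 0.135, with an unadjusted interval roughly 5-20% wider. The direction is certain only if site or subtype is prognostic for MPR. The objection to choosing covariates by baseline tests does not depend on R2. A significant t test would still be sound evidence, so this is an inexpensive improvement and not a flaw that threatens the trial's conclusion.

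**What to change.** - **Primary analysis:** a linear model of MPR on arm, with site and disease subtype as prespecified covariates, reporting the adjusted mean difference and 95% CI. Robust standard errors are a reasonable choice. Keep the t test as a sensitivity analysis.
- **Clinical and PROMIS outcomes:** adjust for the same two factors plus the baseline value of the outcome where Table 1 collects one. No baseline MPR is collected, so none can enter the primary model.
- **Baseline table:** descriptive only. Delete the sentence under which detected differences select variables, and name any further covariates in advance on prognostic grounds. Oral versus subcutaneous route is optional.

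**Cost:** wording only, with no new data. Five degrees of freedom go to the covariates (four for site, one for subtype). If the strata turn out not to predict MPR, almost nothing is lost: simulated power at R2 of zero was 80.2% adjusted against 80.3% unadjusted.
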